## Abstract

**Background:**

High-risk prescribing of non-steroidal anti-inflammatory drugs (NSAIDs) and antiplatelet agents accounts for a significant proportion of hospital admissions due to preventable adverse drug events. The recently completed PINCER trial has demonstrated that a one-off pharmacist-led information technology (IT)-based intervention can significantly reduce high-risk prescribing in primary care, but there is evidence that effects decrease over time and employing additional pharmacists to facilitate change may not be sustainable.

**Methods/design:**

We will conduct a cluster randomised controlled with a stepped wedge design in 40 volunteer general practices in two Scottish health boards. Eligible practices are those that are using the INPS Vision clinical IT system, and have agreed to have relevant medication-related data to be automatically extracted from their electronic medical records. All practices (clusters) that agree to take part will receive the data-driven quality improvement in primary care (DQIP) intervention, but will be randomised to one of 10 start dates. The DQIP intervention has three components: a web-based informatics tool that provides weekly updated feedback of targeted prescribing at practice level, prompts the review of individual patients affected, and summarises each patient's relevant risk factors and prescribing; an outreach visit providing education on targeted prescribing and training in the use of the informatics tool; and a fixed payment of 350 GBP (560 USD; 403 EUR) up front and a small payment of 15 GBP (24 USD; 17 EUR) for each patient reviewed in the 12 months of the intervention. We hypothesise that the DQIP intervention will reduce a composite of nine previously validated measures of high-risk prescribing. Due to the nature of the intervention, it is not possible to blind practices, the core research team, or the data analyst. However, outcome assessment is entirely objective and automated. There will additionally be a process and economic evaluation alongside the main trial.

**Discussion:**

The DQIP intervention is an example of a potentially sustainable safety improvement intervention that builds on the existing National Health Service IT-infrastructure to facilitate systematic management of high-risk prescribing by existing practice staff. Although the focus in this trial is on Non-steroidal anti-inflammatory drugs and antiplatelets, we anticipate that the tested intervention would be generalisable to other types of prescribing if shown to be effective.

**Trial registration:**

ClinicalTrials.gov, dossier number: NCT01425502

## Background

### Importance of high-risk prescribing of non-steroidal anti-inflammatory drugs and antiplatelets

The quality and safety of prescribing in primary care is an area of increasing concern in the UK and internationally. A number of systematic reviews, including large scale studies conducted in the UK, have demonstrated deficits in the safety and quality of medication use to a degree, which constitutes a public health threat: 3% to 4% of all unplanned hospital admissions are caused by preventable adverse drug events [1,2]. Antiplatelets, non-steroidal anti-inflammatory drugs (NSAIDs), oral anticoagulants, diuretics, and other potentially nephrotoxic agents account for approximately 60% of all preventable admissions.

It is important to distinguish 'high-risk' from 'inappropriate' prescribing, because there will be situations where prescribers and patients are struggling to best manage complex problems for which there is no clearly correct action, and high-risk prescriptions may be justified. However, high-risk prescribing requires systematic management and regular review in order to minimise harm. Effective strategies are therefore needed that enable practitioners to continuously identify, review, and monitor high-risk prescribing [3].

One approach to identifying and reducing high-risk prescribing is the assessment of medication use against explicit measures, thereby highlighting patients who are at risk of adverse outcomes and require a review of benefits and risks. In the UK and internationally, this approach is facilitated by the increasing implementation of electronic patient records in primary care, which enable routine screening for patients at risk of preventable adverse drug events. Such an approach requires, as a minimum, focussing on those quality and safety problems that are strongly linked to patient outcomes based on research evidence [4].

Our previous research has defined and validated a broad set of explicit measures for the assessment of prescribing quality and safety in primary care [5]. In accordance with research evidence, the 'use of antiplatelets and oral NSAIDs in patients at increased risk of gastro-intestinal bleeding' and 'use of oral NSAIDs in patients at increased risk of renal failure' were identified as key priorities for quality improvement in primary care by a Delphi panel of primary care clinicians [5]. We have shown that this prescribing is both common and highly variable between practices, which generally indicates scope for improvement [6].

### Rationale for the Data-driven Quality Improvement in Primary care (DQIP) intervention

There is a large body of research examining changing professional practice to improve the quality of care, much of which has been systematically reviewed [7,8]. A significant proportion of this research relates to improving prescribing [9,10]. Although not all studies show positive effects, there is good evidence for small (~5%) to moderate (11% to 20%) effects of a number of quality improvement strategies. Multi-faceted interventions appear to be more effective than single strategy ones. Strategies shown to be effective include the use of:

1. Feedback of performance data [7], particularly if feedback is prolonged rather than one - off [11].

2. Educational outreach visits, where the evidence is particularly consistent for improving prescribing [8].

3. Interactive educational workshops for continuing professional development [12].

4. Informatics to support clinician decision making and implementation of guidelines [13,14], particularly where it is integrated into existing systems [15].

The broad conclusion of this research is that professional practice can be changed, but that improvements in care are not guaranteed with any strategy and are sometimes short-lived. For example, the PINCER trial recently examined the impact of simple feedback versus pharmacists working in general practices for 12 weeks, delivering education and supporting the review of patients with apparent deficiencies in prescribing or monitoring. Significant reductions in all three primary outcome measures at six months follow-up, but for one (high-risk prescribing of NSAIDs in patients with a history of peptic ulcer), the effect size was smaller and non-significant at 12 months, possibly reflecting that the active intervention was one-off and took place early at the start of the follow-up year [16].

With the spread of electronic medical records and improvements in the information technology (IT) infrastructure, it is increasingly feasible to continuously measure prescribing quality and safety. This allows for timely data feedback and enables practices to identify patients who are currently at risk of preventable drug related harm. On the basis of this information, practices can develop a strategy for systematic patient review and monitor trends of high-risk prescribing at practice level that allows unfavourable trends to be exposed and addressed.

### Trial design

The research team will deliver the DQIP intervention to general practices with the intention of changing professional behaviour, and cluster randomisation at practice level will therefore be used. The trial will use the stepped wedge design [17,18], with all participating practices receiving the DQIP intervention, but randomised to one of ten different start dates and with each practice functioning as their own control in a time series analysis. Practices will only have access to the DQIP tool over the duration of the trial (48 weeks), so that outcome measures during the DQIP intervention will be compared to care prior to it. Practices will be randomised to start the intervention at four weekly intervals with planned gaps to avoid Christmas/New Year and March (the end of the QOF reporting year). The stepped wedge design as it is used in this trial is illustrated in Figure 1.

**Figure 1 F1:**
[figure not shown]
**Illustration of the stepped wedge design**. Each rectangle represents an eight-week time period. Practices are randomised to start the intervention in blocks of four, with measurement of outcome for 48 weeks every eight weeks before the intervention starts and during the 48 weeks of the intervention.

## Methods

### Participants and settings

The trial will be conducted in volunteer practices in two Scottish health boards, NHS Tayside and NHS Fife. These two Boards provide healthcare for approximately 700,000 patients, with direct responsibility for hospital and community services, and holding the contracts for independent contractors including general practice. Primary medical care is provided by ~130 general practices, and both Boards have a variety of ways in which they seek to influence general practice prescribing, including the use of formularies, guidelines, newsletters, prescribing advice, and the use of primary care pharmacists.

Prescribing advice and primary care pharmacist input varies significantly between the two Boards. In Tayside, there is a greater primary care pharmacy resource in the sense that each practice has a dedicated (usually part-time) primary care pharmacist who works on a mixture of community health partnership and/or Board priorities, and projects agreed with the practice. In Fife, these functions are split between development pharmacists who work at locality level (five localities across three community health partnerships) providing prescribing advice and facilitated discussion of prescribing data, and primary care pharmacists who work in practices, although typically for fewer hours than in Tayside.

In both Boards, general practitioners (GPs) take responsibility for virtually all community prescribing, although nurses, health visitors, and pharmacists are increasingly prescribing some medicines under defined protocols (although this is currently only a small proportion of total prescribing). The intervention therefore targets existing teams of professionals working in general practices in NHS Tayside and NHS Fife.

### Practice inclusion criteria

Practice inclusion criteria include general medical practices in NHS Fife and NHS Tayside using the INPS Vision clinical IT system (n = 78) and agreeing to participate, and practices that agree to have relevant medication related data to be automatically extracted from their electronic clinical information systems

### Practice exclusion criteria

Practices that use GPASS or EMIS clinical IT systems on the date of randomisation will be excluded, because data extraction for the informatics requires the INPS Vision clinical IT system

### Components of the DQIP intervention

The DQIP intervention has three components (Figure 2).

**Figure 2 F2:**
[figure not shown]
**Illustration of intervention components and desired impact on prescribing behavior**.

Intervention component one: Informatics tool

The informatics tool is central to the intervention, and will involve the extraction of existing GP clinical data to an NHS Tayside database accessible to the DQIP informatics tool developed by Aridhia (an IT company contracted by NHS Tayside for this purpose). The informatics component will:

1. Summarise numbers of patients affected by high-risk prescribing at practice level based on nine validated measures and one composite measure (see outcome measures). This will allow each practice to monitor trends in high-risk prescribing before and after the start of the DQIP intervention.

2. Identify patients affected by high-risk prescribing for review by the practice, and allow practices to select which patients to target first (e.g., patients triggering particular measures, patients triggering multiple measures).

3. Structure clinical information to facilitate review. All decisions about prescribing and organisation of work around DQIP remain a practice responsibility, including deciding which professional is most suited to do any initial record-based review and any follow-up telephone or face-to-face review.

4. Record review decisions using structured data that supports re-identification of patients if necessary, and to measure trial processes for evaluation.

5. Support reminders to practices to review their data via e-mail reminders.

6. Support the educational intervention (provide general information/summaries of the evidence of risk, links to more detailed reference information, prevalence measurement, and run charts for each practice).

The DQIP informatics tool will additionally collect data for trial process evaluation and record data to trigger practice payment at the end of the trial.

The data held in the NHS Tayside database will be identifiable, and access to it will be controlled in the same way that NHS Tayside controls access to all patient identifiable data (e.g., in Central Vision and other web-based patient information systems), with individual user accounts created at the request of each practice. In NHS Tayside, access will be controlled using the standard lightweight directory access protocol (LDAP) account that primary care clinicians use to access all NHS Tayside clinical databases and tools. In NHS Fife, users will receive a Tayside LDAP guest account with access exclusively granted to the DQIP informatics tool (the exception will be practices in North East Fife which use the Ninewells laboratory and already have Tayside LDAP accounts for Central Vision access). Only practice-based users will have access to identifiable patient information in the informatics tool. For DQIP purposes, a practice-based user is defined as a professional that the practice nominates as an appropriate user, and is expected to include GPs, the practice manager, and (in some cases) primary care pharmacists (who are not practice employees, but often work clinically in practices). With practice permission, the research team will have access to aggregate practice data (prevalence and run charts) during the trial for trial management purposes, and to anonymised patient level data after the trial ends for analysis.

### Intervention component two: Educational outreach

The educational intervention will aim to:

1. Clarify the risk of the targeted prescribing and persuade professionals in participating practices that this prescribing is risky by providing general information with references and links to more detailed information.

2. Persuade professionals that the targeted prescribing is a potential problem in their practice by feeding back prevalence via Tables and run charts.

3. Engage professional/internal motivation to do a 'good job' by persuading professionals that the purpose of the intervention is better patient care, and that this is activity that practices should engage in by appealing to professional values and by creating implicit behavioural norms, including through the use of patient and professional stories.

4. Encourage practices to plan and organise the integration of work associated with reviewing targeted prescribing into practice processes, including the definition of responsibilities of different practice members.

The educational intervention will be delivered via an initial educational outreach visit just before intervention start with an offer of a follow-up visit after approximately three months, and via written material available via the DQIP informatics tool (brief reminders when presenting data, links to more comprehensive documents).

### Intervention component three: Financial incentives to review patients

Historically, trials of this nature have included payment to practices for the time taken to participate in the research, paid via NHS Support Costs. Typically, practices are paid based on an estimate of the time involved. For DQIP, we have chosen to structure the 'NHS Support Costs' as an explicit financial incentive to review patients, with payments modelled on existing general practice 'enhanced service' contracts (specific payments beyond capitation for particular services).

Practices will receive a fixed payment of 350 GBP (560 USD; 403 EUR) for participation and providing data, which is paid before the start of the trial. An important aim of this payment is so that practices agreeing to take part have received a payment while waiting to actually start the intervention; in addition, Practices will receive a payment of 15 GBP (24 USD; 17 EUR) per patient reviewed, where practices earn one payment for each patient reviewed in the year of follow-up rather than payment for every review. This payment will be provided at the end of the trial.

It is critical to note is that there is no financial incentive to change prescribing because this remains completely subject to the clinical judgement of the caring clinician after discussion with the patient. The time line of processes that each cohort of practices will receive as part of the DQIP intervention is shown in Appendix 1.

### Recruitment of general practices

General practices with compatible IT systems in the two health boards will be identified through each board's IT department. All eligible practices (practice manager and all general practitioners in each practice) will receive an email, which informs them of the DQIP trial before formal recruitment starts. This email informs practices of the purpose of the trial and of dates and venues of further information meetings to be held in four different locations across Tayside and Fife. The email will be followed by a formal recruitment letter accompanied by an attractive information sheet that summarises trial processes. The letter will be framed as opt-in to study/opt-out of study and an invitation to request a practice visit by the research team or a phone call to discuss. Practices who do not respond to this letter will receive a phone call. From practices that express an interest, we will obtain informed consent to take part, extract data, and randomised each practice to a start date. Up to three months before the start date in each practice, we will confirm consent to take part and to extract data, as well as obtain a list of professionals who are to have access to the informatics tool.

### Recruitment of patient participants

While the DQIP IT tool (intervention component one) will identify patients who are affected by targeted high-risk prescribing, it will be at each practice's discretion whether and when these patients' prescribing is reviewed and how changes in prescribing (if any) are implemented. This may include writing a letter to the patient, inviting the patient to make an appointment for a phone or face-to-face consultation, or to flag the notes to increase awareness of high-risk prescribing the next time the patient attends. All relevant prescribing decisions and follow-up actions will be recorded in the DQIP IT tool and payment for reviews issued, irrespective of the decisions made (see intervention component three: financial incentives).

### Trial objectives

We hypothesise that the DQIP intervention will reduce rates of high-risk prescribing compared to usual practice. The specific objectives are:

1. To test the effectiveness of the DQIP intervention in reducing the specified primary outcome of a composite measure of high-risk non-steroidal anti-inflammatory drug and antiplatelet prescribing.

2. To test the effectiveness of the DQIP intervention in reducing the specified secondary outcomes of: the nine individual measures constituting the composite; related admissions to hospital; repeat versus new prescribing.

3. To assess the cost-effectiveness of the intervention.

### Sample size

In the pilot practices that targeted high-risk NSAID and antiplatelet prescribing, there was a 40% reduction in this prescribing after one round of feedback and review. This is similar to the short-term reduction in high-risk prescribing achieved in the recently completed PINCER trial [16]. We therefore consider a 20% reduction in high-risk prescribing as measured by our outcome measures plausible (and relatively conservative), and have used this in the power calculation. Power calculations for stepped wedge trials are relatively complex, and three estimates are presented.

### Practice level analysis

The first assumes a practice level analysis, which is the most conservative. Estimated standard deviations are taken from the measured SD in the PINCER trial, and baseline was estimated from a general practice clinical dataset. The number of practices required is estimated to detect a 20% reduction from baseline with power of 80% with a two-sided alpha of 0.05 (Table 1).

**Table 1 T1:** Sample size estimation for practice level analysis

Standard Deviation	Difference 10% to 8%	Effect size	Number of practices
4.0%	2.0%	0.500	34
6.0%	2.0%	0.333	73
7.0%	2.0%	0.286	96

### Patient level analysis

The second estimate assumes that patient level before and after data is available, and 15 practices are estimated to be needed. The third assumes a patient level analysis with time series data available, with three 'before' and three 'after' data points. Power is clearly adequate with approximately 10 practices (Table 2).

**Table 2 T2:** Sample size estimation for patient level analysis with time series data

Number of practices	Effect size	Power
10	0.25	83%
10	0.50	97%
10	0.75	99%
10	> 1.0	> 99%

From this analysis, it is clear that lack of power is not likely to be an issue. Because we know that there are significant differences between the two health boards in the primary care pharmacy resource available to practices, we expect to see differences in the effect size between Boards. Additionally, the literature indicates that interventions of the kind planned often (but not always) have varying effects in larger versus smaller practices. This therefore allows us to plan for well powered within strata analyses, and we plan to stratify randomisation into four strata (the combination of the two binary variables Tayside versus Fife and larger versus smaller) with 10 in each strata.

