### Practice level analysis

Practices will be characterised by health board, size, age range, proportion of men and women, number of GPs, and training status. The primary outcome of the composite high-risk prescribing measure (Table 3) will be summarised as the mean and standard deviation across practices for before and after the intervention started. Analysis of before compared to after intervention will be carried out using mixed models or multi-level models that account for the correlation of repeated measures (eight-week periods) and stratification by health board in two levels (Tayside and Fife; larger and smaller list sizes). The primary null hypothesis is no difference in the composite before compared to after intervention. A test of the intervention (before versus after) by health board interaction in the model will test whether results differ by health board. Mixed models have the advantage of allowing for missing data while maintaining the principle of intention to treat (ITT). These models can also incorporate adjustment for baseline differences. The practice level analyses will be secondary to the patient level analyses. This will be repeated for all secondary measures (Tables 4 to 7).

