### Rationale for employing the stepped wedge design

The stepped wedge is a relatively novel design for the evaluation of health service interventions. We have chosen this design for two main reasons. First, the staggered entry of practices into the study has logistic advantages in the delivery of the educational outreach visit. If forty practices are recruited, then four practices will start the intervention every four weeks. In contrast, starting all intervention-arm practices at once under a conventional design is not feasible within the resources of our research team. Second, we anticipated a high dropout rate of practices that would have otherwise been randomised to the 'care as usual arm' under a conventional two arm design, because we would not have been able to provide the same financial incentives to these practices, but would have still required these practices' outcome data. We hope that the fact that all participating practices will receive the intervention will facilitate recruitment and reduce drop-out rates [17].

A welcome side effect of the stepped wedge design is that because practices serve as their own controls, the total sample size required for the trial is lower than under a conventional two-arm design (theoretically, a sample size of ten practices would have sufficed for patient level analysis). Recruiting more practices will support the external validity of findings by ensuring that a more representative range of practices participate and to allow examination by strata.

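### On the protocol's own effect-size scale, the Table 2 powers for 10 practices cannot come from one calculation, so they do not support the claims about ten practices and well-powered strata

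*Protocol article*

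**What the plan says.** The Sample size section plans on a 20% relative reduction: "We therefore consider a 20% reduction in high-risk prescribing as measured by our outcome measures plausible (and relatively conservative"). It presents three estimates.

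- **Practice level (Table 1).** Practices needed to detect a fall from 10% to 8%, "with power of 80% with a two-sided alpha of 0.05 (Table 1"). The SDs are 4%, 6% and 7%: "Estimated standard deviations are taken from the measured SD in the PINCER trial". Effect size is the 2-point difference divided by the SD, as in the row "4.0% 2.0% 0.500 34". The other rows are 0.333 with 73 practices and 0.286 with 96.
- **Patient level, before and after.** 15 practices.
- **Patient level, time series (Table 2).** Three time points on each side of the start, always 10 practices: 83% power at 0.25, 97% at 0.50, 99% at 0.75, and above 99% beyond 1.0. The protocol's reading is "Power is clearly adequate with approximately 10 practices (Table 2"). Table 2 does not define effect size and states no alpha.

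Two conclusions follow from Table 2. The Patient level analysis part of the sample size section says "This therefore allows us to plan for well powered within strata analyses", with 10 practices in each of four strata. The section on the rationale for the stepped wedge design adds "theoretically, a sample size of ten practices would have sufficed for patient level analysis".

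**The concern.** Within Table 2 only the effect size changes; the number of practices and the layout are fixed. For any standard test of a single effect, the ratio of effect to standard error then rises in proportion to the effect size. Doubling the effect from 0.25 to 0.50 should take power from 83% to practically 100%, not to 97%.

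Table 2 is the only one of the three estimates that supports ten practices, and ten is the size of each stratum. If its figures cannot be relied on at the smaller effect sizes, a non-significant result in one stratum could be given more weight than the design can bear.

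**Working it through.** **Inputs.** Table 1: alpha 0.05 two-sided, power 80%, effect sizes 0.500, 0.333 and 0.286. Table 2: 83%, 97% and 99% at 0.25, 0.50 and 0.75 with 10 practices. Assumed for Table 2: the same alpha and the same effect-size scale as Table 1.

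**Step 1: reproduce Table 1.** The paired formula n = ((1.960 + 0.842)/d)² gives 31.4, 70.6 and 96.1, so 32, 71 and 97 when rounded up. The exact paired t version gives 34, 73 and 99. The stated 34, 73 and 96 agree closely with one or the other. This confirms that effect size in Table 1 means difference/SD.

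**Step 2: what each Table 2 row implies.** Absolute power cannot be rebuilt, because the article gives no patients per practice and no correlations. The rows can still be compared with each other. With one design and one alpha, power = Φ(c·d − 1.960), where c is the same in every row. Solving c = (1.960 + z_power)/d:

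- Row 1: (1.960 + 0.954)/0.25 = 2.914/0.25 = 11.66
- Row 2: (1.960 + 1.881)/0.50 = 3.841/0.50 = 7.68
- Row 3: (1.960 + 2.326)/0.75 = 4.286/0.75 = 5.72

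The three values should be equal.

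**Step 3: carry each row across the effect sizes.** For example, row 1 at 0.50 is Φ(5.83 − 1.96) = 99.99%; row 2 at 0.25 is Φ(1.92 − 1.96) = 48%; row 3 at 0.50 is Φ(2.86 − 1.96) = 82%.

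| Row taken as right | 0.25 | 0.286 | 0.333 | 0.50 | 0.75 |
|---|---|---|---|---|---|
| 83% at 0.25 | 83% | 92% | 97% | 99.99% | >99.99% |
| 97% at 0.50 | 48% | 59% | 73% | 97% | 99.99% |
| 99% at 0.75 | 30% | 37% | 48% | 82% | 99% |

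**Step 4: could rounding or another standard test explain it?**

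- Rounding: 82.5% at 0.25 still gives 99.99% at 0.50, and 97.5% at 0.50 gives only 50% at 0.25.
- t test anchored on 83% at 0.25: power at 0.50 is 99.99% with 9 df and still 99.4% with 1 df.
- Log-odds scale with a 10% baseline: 99.98% at 0.50.
- Different alpha: rows 1 and 2 agree only at a one-sided alpha of about 0.51.

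**Step 5: do the other estimates support ten?** The before-and-after estimate asks for 15. On Table 1's basis, a paired t test with 10 practices (9 df, noncentrality d·√10) has about 29%, 16% and 13% power at 0.500, 0.333 and 0.286. The protocol calls that basis the most conservative, so these figures do not predict patient-level power. They show only that the case for ten rests on Table 2.

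**The case against.** The strongest reply is that Table 2 need not share Table 1's scale. It is a different, patient-level calculation and does not define its effect size. On a squared (f²-type) scale, 83% at 0.25 leads to about 98.5% at 0.50 and 99.9% at 0.75, within about 1.5 points of the printed values. If the intervention effect varied between practices with an SD of about 0.7 times its mean, the powers would be 83%, 97% and 98.5%. This stands as a limit on the point: the contradiction is established on the protocol's only stated scale, not on every conceivable one. It does not clear the table. Neither reading appears in the document, the same term means difference/SD in the table immediately before, and the Statistical methods section enters intervention as a fixed term.

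Two further replies also stand in part.

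- A reader might infer that ten practices are too few, or that the trial is underpowered. The document does not support this. If the 83% row is right, the other rows are merely understated. The trial plans 40 practices, and Table 1 asks for 34 at an SD of 4% (though 73 and 96 at 6% and 7%). The remark about ten sufficing is labelled theoretical, and the larger number is justified by external validity as well as by strata.
- A reader might also infer that adjusting for calendar time sharply cuts the printed 83%. The document does not say whether Table 2 allowed for time. Any penalty worked out from the planned six-plus-six windows does not carry over directly to a table built on three plus three, so no reduced figure can be given.

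**Conclusion.** The point holds as an internal inconsistency. Given Table 1's scale and a two-sided alpha of 0.05, the three Table 2 powers cannot come from one calculation; either at least one is wrong or the scale is different and unstated.

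The practical effect depends on the effect size. At 0.50 (the 20% reduction with an SD of 4%), power with 10 practices is about 82% or more whichever printed row is taken as right. At Table 1's other two values for the same reduction, it is 48% to 97% (0.333, SD 6%) or 37% to 92% (0.286, SD 7%). The claim of good power within strata and the claim that ten practices would have been enough are therefore unsupported by the table. They are not shown to be false, and the adequacy of 40 practices for the main comparison is not put in doubt by this inconsistency.

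**What to change.** Recompute Table 2 for the patient-level model that will be fitted, with fixed terms for the eight-week periods and the planned layout of six windows before and six during the intervention (48 weeks / 8 weeks = 6) in place of three and three. State the effect-size scale, alpha, the correlation assumptions and the number of patients per practice, and restate the powers, including at the effect sizes Table 1 links to the 20% reduction.

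Unless the new figures support them, withdraw or soften the statements on well-powered strata and on ten practices sufficing, and describe the analyses within 10-practice strata as exploratory.

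The cost is one recomputed table, a few changed sentences and probably a less favourable stated power within strata. No extra practices are needed, and the randomisation and primary test do not change.
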